### Who will take informed consent?

Potentially eligible patients will normally be referred from their optician or other ophthalmologist to hospital vitreoretinal units, for confirmation and treatment of a FTMH. Patients will usually be approached and consented in these vitreoretinal units. A member of the research team will explain the nature of the study to participants and answer all questions regarding the study, with the aid of a patient information sheet (PIS), and give them sufficient time to decide regarding participation. Typically, this is expected to take a few days. Participants will be informed that their participation is voluntary and will be asked to sign an informed consent form (ICF) prior to any study activities. A copy of the signed ICF will be provided to all participants. An example of the PIS and ICF is included in the appendix.

### Intervention

Eligible patients will be randomised at baseline to one of two treatment arms in a 1:1 ratio through the King’s Clinical Trials Unit (KCTU)’s randomisation platform to either:

PPV, ILM flap and viscoelastic coating without gas tamponade.PPV, ILM peel and 16% C2F6 gas tamponade with 5 days face down posturing.

FTMH surgery will be performed by a trial approved consultant vitreoretinal surgeon, most usually the site’s principal investigator (PI), under local anaesthesia, with or without sedation, or general anaesthesia. Surgery comprises core 23G, 25G or 27G PPV, induction of posterior vitreous detachment if required, and peripheral vitrectomy.

The surgeon’s preferred licensed macular vital stain will be used to stain the ILM.

The gasless surgical technique is based on Stopa *et al*’s description, wherein a hinged ILM flap is created under heavy liquid, then folded over the FTMH. The use of heavy liquid for flap creation is optional and based on surgeon experience and preference. A surgical video is provided in Stopa’s report.^24^

The only deviation from Stopa’s technique is that, where possible, a superior flap should be created, so that gravity helps hold it over the macula. Variations may be necessary as sometimes ILM peeling can be difficult to guide precisely (eg, the discarded flap may be used as the free cover if the folded flap does not position as desired).

A layer of Healon Pro viscoelastic will be applied to the macular area to help hold the flap in place, under heavy liquid. If necessary to retain the flap in position, the flap may be tucked into the hole. Heavy liquid will then be removed. If Healon Pro is not readily available at a study site, then an equivalent Conformité Européenne (CE)-marked OVD licensed for use in the eye may be used, subject to approval from the sponsor.

The aim is to seal the hole with ILM/viscoelastic, as our mechanistic hypothesis is that fluid flow through the hole maintains patency. However, tamponade will be used if it is not technically possible to occlude the hole using a combination of ILM and OVD.

Those randomised to standard vitrectomy will have the same surgery including a single, approximately 1 disc diameter circular ILM peel centred on the hole, but this will be discarded, and 16% C2F6 tamponade injected into the eye. ILM peeling has been chosen as the single technique for the standard of care arm, as it is still the most common technique in the UK for managing FTMHs.^30^ C_2_F_6_ has been selected as UK practice surveys indicate it is the most commonly used FTMH tamponade.^14^

In both arms, sclerotomies can be sutured if the surgeon deems it necessary.

Surgery will be video recorded (included in consent), and the duration will be recorded for all operations. Both arms will be seen 1 day, 1 week and 1, 3 and 6 months postoperatively.

Repeat surgery with vitrectomy and gas for non-closed holes will be allowed and considered a ‘failure’.

Other surgical steps will be those routinely used by the operating surgeon, or as needed to deal with any complications, such as cryotherapy and gas for a retinal tear.

#### Postoperative eye therapy

Broad-spectrum antibiotics eye drops will be prescribed for at least 1 week after surgery, and topical steroid eye drops for at least 4 weeks postoperatively. Mydriatics are allowed at the surgeon’s discretion, for approximately 1–2 weeks. The choice of steroid, antibiotic and mydriatic is at the surgeon’s preference, also considering any local policy and the particulars of each participant. Postoperative antiglaucoma medications are also permitted as required, at the surgeon’s discretion.

Patients should be provided with standard postoperative instructions and those relevant to their case, such as avoiding flying if they have gas in their eye.

#### Postoperative positioning

Participants in the standard vitrectomy arm with gas tamponade will require postoperative posturing. Participants in this arm should be advised to posture face down overnight following surgery, then face down by day for 50 mins/hour, sleeping opposite cheek to pillow, for 5 days. Participants are also advised to avoid lying on their backs or leaning backwards for 5 days after surgery. To standardise the protocol for all sites, face down posturing is being used for all hole sizes receiving gas tamponade.

Participants in the novel surgery arm will not be required to posture postoperatively.

### Relevant concomitant care permitted or prohibited during the trial

#### Cataract surgery including combined phacovitrectomy

Phacoemulsification and IOL implant can be performed prior to vitrectomy in a ‘combined procedure’ if deemed appropriate, but the decision to undertake phacoemulsification must be made and documented prior to randomisation. If an unplanned cataract occurs during surgery (eg, if there was lens touch and loss of fundal view), then this should be recorded as a deviation. Subsequent cataract surgery is allowed, but deferred until after month 3 unless clinically urgent, in which case it should be recorded as a deviation.

### Strategies to improve adherence to interventions

Participants will be provided with a standardised document detailing the postoperative posturing required for those in the arm receiving standard surgery with gas tamponade. As part of the surgical consent process, investigators are required to explain the post-operative positioning regimen.

### Outcomes

The main aim of the trial is to establish the feasibility of a subsequent pivotal trial, while also collecting provisional safety and efficacy data. To reflect this, the outcomes are divided as follows:

#### Feasibility outcomes

Screen failure (proportion of those screened).Recruitment rate (participants per site per month).Participant retention (proportion reaching month 6 milestone).Cross-over (proportion converting to standard vitrectomy with gas, due to inability to seal the FTMH, or detection of peripheral retinal breaks).

#### Efficacy outcomes

Refracted ETDRS BCVA at 6 months (mean change in ETDRS letter score from baseline).Surgical success (proportion with FTMH closure within 3 months without further FTMH surgery).Area under the BCVA versus time curve (ETDRS letter score).

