### Statistical methods

#### Statistical methods for primary and secondary outcomes

The proportion of patients who are successfully recruited after screening will be reported with 95% CIs computed by the exact binomial method, as will all outcomes assessing feasibility except for recruitment rate, which will be reported per site per month. In addition to summary statistics of the secondary outcomes (similarly to the primary and baseline outcomes), all harms and withdrawals will be reported with 95% CIs.

An exploratory efficacy analysis will be based on intent-to-treat and include all randomised participants. A secondary analysis will be per protocol comparing those who had gasless vs standard surgery, irrespective of allocation, to investigate the effect of cross-over. The safety population will include all participants who underwent randomisation.

The proportion of participants with primary surgical anatomical closure and mean BCVA (change from baseline, and area under the curve (AUC)) will be compared between groups at 6 months (Fisher’s exact test and Mann-Whitney, respectively). For the AUC analysis, VA will often be below 1 ETDRS letter when gas is in the eye, so ETDRS acuity will be converted to logarithm of the minimum angle of resolution (logMAR) with assignment of logMAR values to count fingers or worse^36^:

Count fingers at 2 ft: logMAR+1.85.

Hand motions at 2 ft: logMAR+2.3.

Visual acuity of ‘light perception’ or ‘no light perception’ will not be converted and will be reported separately.

Adherence to posturing and treatment acceptability will be described.

The MacTSQ has been validated for use in macular diseases requiring drug administration and consists of two subscales: information provision/convenience and treatment satisfaction.^35^ The individual scores from each subscale as well as the composite score will be analysed based on change from the first time point (paired sample t-test) and between groups (analysis of variance model).

Quantifiable findings from the MacTSQ will be analysed using descriptive statistics. Open-ended responses will be analysed for descriptive and analytic accounts using thematic analysis and a constant comparison approach. Analysis will pay particular attention to key factors that impact on patient experiences both positively and negatively and will integrate quantifiable data from the MacTSQ in the analysis to investigate patterns of experience within the participant population.

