### Methods for additional analyses

Prespecified exploratory subgroup analyses will be performed according to the following variables:

Operation performed; vitrectomy versus combined phacovitrectomy.The choice of whether to perform vitrectomy alone or combined with phacoemulsification will be examined, as the decision to remove the cataract at the same time as surgery may positively affect visual recovery and final acuity. Performing combined cataract surgery may impact on macular hole closure rates with the new technique.Macular hole size: small (≤250 µm), medium (251–400 µm), or large (>400 µm).Anatomic closure is known to be affected by the MLD of the FTMH. Outcomes will be analysed, subgrouped by categorical hole size to determine what effect it has with the novel technique.Lens status; phakic versus pseudophakicVisual outcomes may vary depending on the lens status at the beginning and end of the trial. Emerging or pre-existing cataract, if untreated, may limit BCVA improvement, compared with pseudophakic participants.Surgical learning curve; each surgeon’s first five cases versus subsequent cases.To investigate the role of the surgical learning curve on the outcome of the study, the success of the first five cases of novel gasless surgery that each surgeon performs will be compared against any subsequent cases. This will inform a descriptive analysis of the learning curve for the surgical technique, with an intention to perform a cumulative sum curve if an individual surgeon performs sufficient cases to inform the analysis.Vitreomacular status; vitreomacular traction versus no vitreomacular traction.Primary anatomical closure may be related to the VMT status at the time of surgery. Understanding the impact of VMT may help refine case selection for any subsequent pivotal trial.Duration of macular hole symptoms: Either more or less than the median duration, or more or less than 4 months.FTMH duration is known to influence both primary anatomical success and final BCVA following standard surgery. This subgroup analysis will help determine if this applies to the new surgical approach and help understand the generalisability of the results.

These factors will be applied as effects to the clinical efficacy outcomes.

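### A gasless-arm eye that cannot be sealed, is given gas at the first operation and then closes counts as a surgical success, so the closure results do not register inability to seal

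*Protocol article*

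**What the plan says.** All references are to the protocol article.

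- **Efficacy outcomes.** The closure outcome is "Surgical success (proportion with FTMH closure within 3 months without further FTMH surgery". Gas at the first operation does not enter the definition.
- **Intervention, gasless arm.** "tamponade will be used if it is not technically possible to occlude the hole using a combination of ILM and OVD". This happens within the first operation.
- **Intervention, later rescue.** "Repeat surgery with vitrectomy and gas for non-closed holes will be allowed and considered a" failure. Conversion during the first operation is not given that label.
- **Feasibility outcomes.** Conversion is an outcome of its own: "Cross-over (proportion converting to standard vitrectomy with gas, due to inability to seal the FTMH, or detection of peripheral retinal breaks". The two reasons form one proportion.
- **Statistical methods.** "An exploratory efficacy analysis will be based on intent-to-treat and include all randomised participants". Then: "A secondary analysis will be per protocol comparing those who had gasless vs standard surgery, irrespective of allocation, to investigate the effect of cross-over". Feasibility proportions, including cross-over, get exact binomial 95% CIs.
- **Methods for additional analyses.** The learning curve compares "the success of the first five cases of novel gasless surgery that each surgeon performs" with later cases. Outcomes are also subgrouped by hole size, to see how size acts with the novel technique.

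**The concern.** An eye that cannot be sealed with membrane and viscoelastic is an eye in which the gasless technique did not work. The closure results have two places to put it. Under intent-to-treat it stays in the gasless arm and, if the gas closes the hole, it is a success. Under the analysis by surgery received it leaves the gasless denominator and joins the standard group. In neither is it a gasless failure.

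The same gap reaches two analyses meant to shape a pivotal trial. In the learning curve, the article does not say whether a converted operation is a case of gasless surgery performed. Converted early cases would either score as successes when they close or drop out, and either way the curve flattens. In the hole-size subgroups, if larger holes convert more often (an assumption), gas could close them and hide the pattern. The Discussion gives effectiveness confined to holes below a certain size as an example of a result that would bear on whether to proceed.

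**Working it through.** **Plan's own figure.** The article states no conversion rate, no closure rate with gas and no power for closure. Its sample size is 60 in total, for at least 28 per group with 7% attrition: 60 × 0.93 = 55.8, about 28 per group. That figure is not in question. It is used here only for 30 eyes per arm.

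**Inputs.**
- Closure when gasless surgery is completed, g: 90% assumed. The Background gives 91.7% to 100% in five case series and 80% in a sixth.
- Closure after conversion to gas, k: 95% assumed.
- Proportion converted, c: 0% to 30% assumed.

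**Formulas.**
- Success as defined, intent-to-treat: (1 − c) × g + c × k
- Gasless closure by surgery received: g
- Gas-free closure among all allocated to gasless: (1 − c) × g

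| Converted | Intent-to-treat success | By surgery received, gasless | Gas-free closure |
|---|---|---|---|
| 0% | 90.0% | 90% | 90% |
| 10% | 90.5% | 90% | 81% |
| 20% | 91.0% | 90% | 72% |
| 30% | 91.5% | 90% | 63% |

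At 20%: 0.8 × 0.90 + 0.2 × 0.95 = 0.72 + 0.19 = 0.91, against 0.72. In 30 eyes that is about 27/30 (exact 95% CI 73.5% to 97.9%) against 22/30 (54.1% to 87.7%).

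**Sensitivity to the assumed rates, at 20% conversion.**
- g = 91.7%, k = 95%: 92.4% against 73.4%.
- g = k = 90%: 90% against 72%. Intent-to-treat success is flat in c.
- g = 100%, k = 95%: 0.80 + 0.19 = 99% against 80%. Intent-to-treat success falls slightly with c.

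The gap between the two measures is c × k in every case. Only the direction in which the intent-to-treat figure drifts depends on whether k exceeds g.

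**Does the endpoint still detect poor gasless surgery?** Power of Fisher's exact test, taking two-sided 5%, 30 per arm and 95% control closure as assumptions. With 6 of 30 converted, the gasless-arm rate is (24 × g + 6 × 0.95)/30.

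| True closure after completed gasless surgery | Power, none converted | Power, 6 of 30 converted |
|---|---|---|
| 50% | 98% | 91% |
| 60% | 89% | 73% |
| 70% | 63% | 44% |
| 80% | 24% | 14% |

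Conversion weakens detection but does not remove it.

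**Hole size.** At least 16 large holes are planned, so about 8 per arm under 1:1 allocation. If 2 of 8 convert and all 8 close, success as defined is 8/8, by surgery received 6/6, and gas-free closure 6/8.

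**The case against.** Five points can be made for the plan.

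1. **Intent-to-treat closure is a legitimate estimand.** It measures the strategy the article describes, gasless surgery with gas as back-up, and it applies to both arms alike. A no-gas definition cannot apply to controls. This stands. The comparison should stay, and the addition is a one-arm description.
2. **Conversion is already reported.** Cross-over is a feasibility outcome with an exact CI, so 6 of 30 would appear as 20% (7.7% to 38.6%). This stands in large part. But inability to seal is pooled with peripheral breaks, which are not a failure to seal.
3. **Gas-free closure can largely be derived.** If no control eye receives gasless surgery, closed eyes in the gasless group by surgery received, divided by all eyes allocated to gasless, give the figure. True. What is missing is the stated summary, its interval, the split by reason, and its use in the subgroup and learning-curve analyses.
4. **Treating later rescue differently is defensible.** It is a second operation and conversion is not. Agreed, so this is not a contradiction in the article.
5. **The SAP may deal with this.** It is said to exist and is not shown. The point therefore rests only on the outcome definition and the analysis sets that the article itself states.

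A reader might also infer that converted early cases are sure to score as successes in the learning curve. The article does not settle that, because they may instead be dropped.

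**Conclusion.** The point holds in a limited form. By the article's wording, a converted gasless-arm eye that closes is an intent-to-treat success, and the analysis by surgery received moves it out of the gasless group. The stated closure results therefore do not register inability to seal. At 20% conversion the illustration gives 91% against 72%. Both closure rates and the conversion rate are assumptions, and the size of the gap is close to the conversion rate itself.

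A reader might infer that the endpoint cannot show failure of the gasless technique. The document does not support that. An eye that stays open, or needs repeat surgery, after completed gasless surgery is a failure under the definition, and a converted eye is a success only if it closes. Nor does success necessarily rise with conversion, since that requires gas to close more holes than completed gasless surgery.

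Closure is exploratory in a 60-participant feasibility trial, and the decision on a pivotal trial is to rest on the results taken as a whole. This is a minor-to-moderate improvement.

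**What to change.** 1. Keep the intent-to-treat closure comparison and describe it as an estimate for gasless surgery with gas as back-up.
2. Add a supplementary descriptive summary for all participants allocated to gasless surgery: hole closed within 3 months, no gas at the first operation and no further macular hole surgery, with an exact 95% CI.
3. Report conversions by reason, inability to seal separately from peripheral breaks. In the new summary, conversion for inability to seal counts as not successful. Show conversion for a break both ways, once as not successful and once scored on its closure result.
4. Use this definition, with converted eyes kept in the denominator, for the learning-curve and hole-size analyses of the gasless arm.

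The surgical rule on when gas is used is not questioned.

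The cost is a few lines of SAP wording and one extra table. The cross-over outcome names both reasons, so the data should already be collected. The price is a less favourable rate for gasless surgery beside the intent-to-treat figure.

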#### Safety outcomes

Adverse events (AEs).Intraoperative and postoperative complications.Development or progression of lens opacity within 6 months of vitrectomy (proportion undergoing or listed for cataract surgery and mean change in Lens Opacities Classification System 2 (LOCS2) grading).

#### Patient-reported outcomes measures

Participant acceptability of the intervention assessed by the Macular Disease Treatment Satisfaction Questionnaire (MacTSQ; composite score).National Eye Institute 25-Item Visual Function Questionnaire (NEI VFQ25; composite score).Qualitative analysis of participant feedback.

### Participant timeline

A summary of the trial is shown in figure 1.

**Figure 1 F1:**
[figure not shown]
Study flow chart. C_2_F_6_, hexafluoroethane; FTMH, full-thickness macular hole; MacTSQ, Macular Disease Treatment Satisfaction Questionnaire; n, number; NEI VFQ-25, National Eye Institute 25-Item Visual Function Questionnaire.

Screening will occur once the participant has given their written informed consent, and surgery defines the baseline visit. Participants will be randomised at the time of screening once the investigator has confirmed eligibility and a decision has been made regarding combined surgery.

Participants will be seen for follow-up according to a typical standard of care, with appointments at day 1, week 1, month 1, month 3 and month 6. A summary of the trial procedures at each appointment is included in table 1.

**Table 1 T1:** Schedule of study assessments, summary of visit activities

Activity	Screening	Baseline	D1	W1	M1	M3	M6
Visit window (±days)	Day −42 to 0	–	0	±3	±7	±7	±7
Consent	X						
Medical and ophthalmic history	X						
Randomisation	X						
Vitrectomy		X					
Full refracted ETDRS BCVA	X					X	X
Clinic ETDRS VA*			X	X	X		
Service user questionnaire (posturing compliance)			X	X			
Macular Disease Treatment Satisfaction Questionnaire			X	X	X	X	X
Visual Function Questionnaire 25-Item	X						X
Slit-lamp examination and IOP	X		X	X	X	X	X
Lens grading	X		X	X	X	X	X
OCT (if possible)†	X		X†	X†	X	X	X
Adverse events (safety)	X	X	X	X	X	X	X
Concomitant medications	X	X	X	X	X	X	X

* Clinic ETDRS VA should be undertaken in the study eye only using an ETDRS chart with correction of any refractive error, with and without. pinhole. This should be undertaken by unmasked assessors at day 1, week 1 and month 1 in both arms. Thereafter from month 3, only suitably trained and delegated masked assessors should undertake Full refracted ETDRS BCVA.

† OCT at the ‘day 1’ and ‘week 1’ visits may not be possible in those receiving gas tamponade and may be omitted at these two visits for participants in the control arm. OCT must be performed in the study eye for all participants at all other visits, and at the day 1 and week 1 visits for those in the novel surgery arm.

BCVA, best-corrected VA; ETDRS, Early Treatment Diabetic Retinopathy Study; IOP, intraocular pressure; OCT, optical coherence tomography; VA, visual acuity; VFQ-25, National Eye Institute 25-Item Visual Function Questionnaire.

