### Who will be blinded?

BCVA and central optical coherence tomography (OCT) assessors will be masked to study treatment allocation. Due to the presence of gas within the eye, it is not possible to mask participants, and while still in the eye, it is also not possible to mask BCVA assessors. Hence, the BCVA assessments on day 1, day 7 and month 1 will be performed by an unmasked assessor, as the gas will probably be present at these visits. The assessment of OCT images at a site level is not masked, but a masked grader will assess OCT images sent to an independent reading centre, to determine the OCT-based efficacy outcome measure (anatomic closure).

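### The last posturing-compliance questionnaire may be completed from day 4, before the 5-day posturing period has ended, so adherence may not cover the same period for every gas-arm participant

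*Protocol article*

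**What the plan says.** Four parts of the protocol article bear on this point.

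- **Regimen.** The Intervention section defines the control arm as including "16% C2F6 gas tamponade with 5 days face down posturing". Postoperative positioning gives the detail: "face down overnight following surgery, then face down by day for 50 mins/hour, sleeping opposite cheek to pillow, for 5 days". It also tells participants to "avoid lying on their backs or leaning backwards for 5 days after surgery".
- **Collection.** In Table 1 the row "Service user questionnaire (posturing compliance") is marked at day 1 and week 1. It is blank at months 1, 3 and 6.
- **Timing.** The Table 1 row "Visit window (±days") gives 0 for day 1 and ±3 for week 1. The masking section places the week 1 visit on day 7: "the BCVA assessments on day 1, day 7 and month 1 will be performed by an unmasked assessor". Visits are counted from surgery.
- **Use.** The statistical methods section commits to a result: "Adherence to posturing and treatment acceptability will be described".

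Nothing in the article requires the week 1 visit, or the questionnaire, to follow the end of posturing.

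**The concern.** A descriptive adherence figure is easy to interpret only if every participant is observed over the same period. Here the second questionnaire is the only scheduled record of daytime posturing, because the day 1 form can cover no more than the first night. If the week 1 visit falls early in its window, the form is completed while the regimen is still running, and the schedule offers no later chance to record the rest. Participants seen from day 6 onwards report on the whole regimen; those seen earlier do not.

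The item matters somewhat to this trial. The Background reports that up to half of patients comply poorly with posturing, and the burden of posturing is one of the main reasons for testing gasless surgery. A pivotal trial would want to know how fully the control regimen was followed. Analysis cannot repair the gap afterwards: on day 4 the remaining posturing has not yet happened, so neither the wording of the recall question nor a rule in the analysis plan can recover it.

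**Working it through.** The plan states no figure to reproduce. The check is a comparison of days.

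**Inputs**

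- Nominal week 1 visit: day 7 (masking section).
- Week 1 window: ±3 days (Table 1).
- Posturing: 5 days (Intervention; Postoperative positioning).
- Gas-arm size: 60 participants randomised 1:1, so 60 / 2 = 30.

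**Step 1: visit window.** It opens on day 7 − 3 = day 4 and closes on day 7 + 3 = day 10. That gives 7 permitted days: 4, 5, 6, 7, 8, 9 and 10.

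**Step 2: last posturing day.** The text can be counted in two ways, so both are shown.

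| Count | Posturing days | Permitted visit days on or before the last posturing day | Share of window |
|---|---|---|---|
| Surgery = day 0, not counted | 1–5 | 4 and 5 | 2/7 = 29% |
| Day of surgery counted | 0–4 | 4 | 1/7 = 14% |

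**Step 3: how much goes unrecorded.**

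- Under the first count, a day 4 visit misses the rest of day 4 and all of day 5. That is between 1 and 2 of the 5 days, or 20–40%. A day 5 visit misses at most part of the last day.
- Under the second count, a day 4 visit misses at most part of the last day.
- Visits on days 6 to 10 cover the whole regimen under either count.

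**Step 4: number of participants.** This depends on when visits actually take place, which the article does not report.

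- All visits on day 7: 0 affected.
- Visits spread evenly over the window (an assumption): 1/7 × 30 = 4.3 under the second count and 2/7 × 30 = 8.6 under the first, so about 4 to 9 participants.

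**Step 5: earliest safe day.** Posturing ends on day 5 at the latest, so a form completed on or after day 6 covers the full period under both counts.

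**The case against.** The strongest reply is that this matters little. A ±3-day window around a one-week visit is ordinary, a visit on the nominal day captures everything, and 5 or 6 of the 7 permitted days are unaffected. Posturing adherence is not among the listed feasibility, efficacy, safety or patient-reported outcomes, nor among the prespecified subgroup variables. It is described and not tested, and no decision rule uses it. All of this stands, and it is why the point is minor.

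A second reply is that the article condenses a fuller protocol, and that the questionnaire, its recall period and its completion instructions are not shown. It is fair that the trial may already complete the form later than the table implies. So the point is limited to what the published schedule allows: it fixes both the collection visits and the window, and together they permit a form completed before posturing ends.

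Two stronger readings are tempting, and the documents support neither.

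- **That adherence would be overstated.** A reader might infer this by supposing that participants lapse most towards the end. The article gives overall figures for poor compliance and discomfort but no pattern over time, so the direction of any bias is unknown.
- **That control-arm closure could not be interpreted.** The plan contains no analysis relating closure to adherence, so no planned result fails in that way.

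**Conclusion.** The point holds as a minor weakness in measurement timing. On the article's own figures, a visit fully within the permitted window can precede the end of posturing, or fall on its last day if the day of surgery is counted, and nothing later fills the gap. The consequence is that the adherence to be described may not refer to the same period for all gas-arm participants.

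The participant range shown in the working rests on two assumptions: 30 participants in the gas arm, and, for its upper part, visits spread evenly over the window. Clustering around day 7 would bring the number close to zero. The finding does not rest on any view about adherence over time, and it implies nothing about how long posturing should last. The feasibility conclusions and the clinical comparisons are not threatened.

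**What to change.** Leave the week 1 visit window and the posturing regimen unchanged. Add one footnote to the posturing-compliance row of Table 1 stating that the second questionnaire:

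- is completed on or after day 6;
- asks about the whole posturing period; and
- records the date on which it was completed.

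If the week 1 visit takes place before day 6, the form is completed by phone or returned by post.

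The cost is the footnote, a date field on the form if it lacks one, and an occasional call or posted form for participants seen on day 4 or 5. No extra visit is needed. A small drawback is that a posted form may not come back; the completion date will show which participants have a full-period record, and the report can state how many do.
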